#### Secondary outcome measures

##### Active pain-free range of motion (AROM)

AROM will be assessed for flexion, abduction [36], external rotation [37] and hand behind back [38]. All measurements will be conducted to the onset of pain and evaluated by an inclinometer (Baseline® Bubble Inclinometer, Enterprises Inc). Measurements will be taken at baseline and the end of the treatment period. Limitations in AROM might affect the ability to carry out activities of daily living in patients with RCRP [39] and, therefore, determining changes as a result of a treatment programme might be clinically relevant.

##### Pain pressure threshold (PPT)

Measurements will be collected at three different sites: 5 cm distal to the lateral border of the acromion on both sides over the deltoid muscle, and 10 cm distal to the tibiofemoral joint line, over the tibialis anterior muscle on the unaffected side [40]. The importance of having a psychophysical measurement of general mechanical sensitivity is in helping to explore whether there are differences in pain, function, general pain pressure threshold and treatment outcomes in different groups. A calibrated digital algometer (Wagner instruments, model FPX 25) will be utilized for assessments. Three measurements with an interval of 30 s will be taken. PPT will be assessed at baseline and end of the treatment period. This outcome measure will be analysed in a separate publication.

##### Global rating scale of change (GROC)

GROC is a psychometric instrument that assesses the perception of improvement or deterioration from the patient’s perspective [41]. The scale to be used in this study involves a 15 point Likert scale, ranging from − 7 (much worse) to + 7 (completely recovered). Using this scale, the participant will respond to the following question: “Regarding your shoulder problem, how do you assess your shoulder condition since your entry in the study”. Despite evidence of instability in this scale [42], it is important to allow the participant to make an overall assessment of their condition as a result of the treatment delivered. The assessments will be taken at the end of treatment period and at the final follow-up. Previous research have adopted a value of + 5 as a cut-off point to consider that treatment was sucessful [26].

##### Expectations

In health sciences, this construct assesses the beliefs that a patient has in relation to several aspects of implementation and results of therapeutic modalities [43]. Hence, expectations can be positive, negative or neutral. Factors such as a desire that something happens, previous experiences, reports from significant others, are a few of the aspects taken into account when making a prejudgment regarding a therapeutic encounter [44]. Recently, Chester and colleagues [45] investigated multiple putative factors associated with improved function and reduced pain at the end of physiotherapy treatment for people with shoulder pain. One of the strongest predictors found was the patient’s expectation of recovery. Therefore, assessment of expectation in patients with shoulder pain seems important. In this study, the participant will be asked to answer the following question: “How much do you expect your shoulder problem to change as a result of physiotherapy treatment?” A seven point Likert scale ranging from “completely recovered” to “worse than ever” will be used. Commonly, expectations are assessed prior to the start of a treatment programme. In this study, we will assess it at the beginning of the study and after 3 weeks of treatment. We understand that expectation is a dynamic construct that might vary throughout time and its assessment in two different time points may provide important inferences to be made afterwards.This outcome measure will be analysed and reported in a separate publication.

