##### Self-efficacy (SE)

SE relates to one’s beliefs that he or she is capable of dealing and executing a certain course of action needed to manage actual and / or prospective events [46]. In health sciences, SE is related to pain and long term incapacity [47], fear of movement [48], and in patients with shoulder pain, is an important factor associated with better therapeutic outcomes [45, 49]. The domains of pain and physical function of the validated Brazilian version of the chronic pain self-efficacy scale will be used in this research [50]. SE will be assessed at baseline, end of the treatment period and on follow-up.

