### Participant timeline

The enrollment process will begin from the end of February 2020. After entering the study, participants will have the following outcomes assessed at baseline: SPADI, NPRS, AROM, PPT, expectations and SE; at the end of the treatment period: SPADI, NPRS, AROM, PPT and GROC; and at one month follow-up: SPADI, NPRS, and GROC. Expectation is the only outcome measure to be collected during the third week of treatment. Figure 2 depicts enrolment, interventions and assesssments timeframes throughout the study. Participants will attend ten individual sessions, twice a week (approximately 40 min each), in either of the available treatment sites, according to their geographic locations (see study settings). For the follow-up, participants will be contacted by a research member via email or mail to fill out the respective outcome measures. A telephone call will be made for participants that miss one treatment session without providing explanations.

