### Sample size

In order to calculate the number of subjects to be included in this study an alpha value of 0.05 and power of 80% was chosen together with a minimal clinically important difference of 10 points on the SPADI scale with standard deviation of 13.5 points [26]. An initial number of 28 participants in each group was required based on this calculation. With an estimated 20% loss to follow-up, we planned to recruit a total of 70 subjects (35 in each group).

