### Statistical analysis

Data will be analysed using the Statistical Package for Social Science software (SPSS v.20, Inc., Chicago, USA). The analyses will be conducted considering a statistically significant *p*-value ≤0.05. Data normality of the study will be assessed with the Kolmogorov-Smirnov test and homogeneity with the Levene’s test. The results will be reported as the mean with corresponding 95% confidence interval. Intention-to-treat analysis will be conducted so that all patients are analysed within their group allocation. Drop-outs and their reasons will be informed. All data input will be kept in two different files (double data entry) that will be updated every week by a research assistant.

A two-way analysis of variance will be conducted to assess between and within groups differences. For the primary outcome measures (SPADI and NPRS) a 2 × 3 ANOVA with treatment group (EG versus CG) and time (baseline, end of the treatment and follow-up) factors will be performed. Separate 2 × 2 ANOVA will be used for ROM (baseline and end of the treatment period), and a 2 × 3 ANOVA will be conducted for self-efficacy (baseline, end of the treatment period and follow-up). Additionally, appropriate post-hoc tests (Bonferroni) will be used if prior analysis indicates significant differences. GROC analysis will be conducted using descriptive statistics and participants will be classified according to treatment success. Those reporting + 5 or more will be classified as successful. Within groups differences will be calculated at the end of the treatment period and follow-up, and effect sizes will be calculated using Cohen effect size (0.2–0.5: small effect, 0.5–0.8: moderate effect, 0.8 or more: large effect size).

A second study will explore changes in expectation throughout treatment descriptively and whether those differences are associated with SPADI, NPRS and group allocated. Therefore, an ANCOVA will be conducted to analyze the influences of covariates (expectation and self-efficacy) on SPADI and NPRS. A separate 2 × 3 ANOVA will be used to examine PPT measurements in the three different body areas. Post-hoc tests (Bonferroni) will be used if prior analysis indicates significant differences.

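### Baseline expectation and self-efficacy, which the protocol itself calls prognostic, are left out of the primary SPADI and NPRS comparison: a missed, inexpensive chance of precision, not an error

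*Protocol article*

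**What the plan says.** All references are to the protocol article.

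- **Expectations:** of the factors associated with function and pain at the end of physiotherapy for shoulder pain, "One of the strongest predictors found was the patient’s expectation of recovery". Function and pain are the primary outcomes in Table 2.
- **Self-efficacy (SE):** in patients with shoulder pain, self-efficacy "is an important factor associated with better therapeutic outcomes". Two domains of the scale are used, pain and physical function.
- **Participant timeline:** the baseline assessments are "SPADI, NPRS, AROM, PPT, expectations and SE".
- **Allocation:** randomisation is stratified by pain only.
- **Statistical analysis:** the primary SPADI and NPRS analysis is a 2 × 3 ANOVA with group and time as its factors and no covariate named. A second study then follows, in which "an ANCOVA will be conducted to analyze the influences of covariates (expectation and self-efficacy) on SPADI and NPRS". The text does not say whether that model uses the baseline or the third-week expectation value.

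**The concern.** The plan identifies two predictors of its own primary outcomes, collects them before treatment and intends to model SPADI and NPRS on them, but keeps them out of the stated MWM versus sham comparison. Neither is balanced by the stratification. With 28 to 35 participants per arm, a moderate chance difference between arms in such a variable is common. Whatever outcome variance the two measures explain also stays in the error term. At stake is some precision in a small trial, and a prespecified answer to any baseline imbalance that appears. An adjustment chosen after an imbalance has been seen is open to challenge.

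**Working it through.** **Inputs.** From Sample size: "an alpha value of 0.05 and power of 80% was chosen"; a "minimal clinically important difference of 10 points on the SPADI scale" "with standard deviation of 13.5 points"; and "An initial number of 28 participants in each group was required based on this calculation". The same section allows 20% loss and plans 35 per arm. Sidedness is not stated; two-sided is assumed. The documents give no correlation or R² for either covariate, so both are assumed over a range.

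**1. The plan's own figure.** n per arm = 2 × (1.960 + 0.842)² × (13.5/10)² = 28.6. This is 29 when rounded up, against the stated 28, close enough to count as reproduced. 28/(1 − 0.20) = 35 per arm, 70 in total. The sample size therefore assumes no covariate gain.

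**2. Unadjusted power at 28 per arm.** SE = 13.5 × √(2/28) = 3.608; noncentrality = 10/3.608 = 2.772; 54 degrees of freedom. Power = 77.7% by noncentral t (79.1% by normal approximation).

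**3. Power with two covariates.** Let R² be the share of the remaining outcome variance that the two explain, with 13.5 taken as the SD left after the baseline score. Two costs are charged: two degrees of freedom (54 to 52) and a variance inflation of 1 + 2/51 for estimating two slopes. Then SE = 13.5 × √(1 − R²) × √(2/28 × (1 + 2/51)). The CI half-width is SE times the t quantile (2.005 on 54 df, 2.007 on 52 df).

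| Assumed R² | SE | 95% CI half-width | Power |
|---|---|---|---|
| unadjusted | 3.608 | 7.23 | 77.7% |
| 0% | 3.678 | 7.38 | 76.1% |
| 3% | 3.623 | 7.27 | 77.3% |
| 5% | 3.585 | 7.19 | 78.2% |
| 10% | 3.489 | 7.00 | 80.3% |
| 15% | 3.391 | 6.80 | 82.5% |
| 20% | 3.290 | 6.60 | 84.7% |

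The SE breaks even where (1 − R²) × 53/51 = 1, that is R² = 0.038. With the lost degrees of freedom, the break-even for power is about 4%.

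**4. Three terms instead of two.** If both self-efficacy domains enter separately (51 df, inflation 1 + 3/50), power is 77.3% at R² = 5% and 79.5% at 10%.

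**5. Chance imbalance.** The standardised baseline difference in any one covariate has SD √(2/n): 0.267 at n = 28 and 0.239 at n = 35. A difference of at least 0.3 SD in either direction then occurs in 26% and 21% of randomisations. At an assumed correlation r with outcome, it moves the SPADI difference by 0.3 × r × 13.5: 0.8, 1.2 and 1.6 points for r = 0.2, 0.3 and 0.4. The middle value is 12% of the 10-point target and one third of the SE in step 2.

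**6. How a covariate must enter.** Baseline is a level of the time factor, so the treatment effect is the group-by-time interaction, a between-group difference in change. A covariate entered only as a main effect adds the same b × x to a participant's baseline and later scores, and in the change it cancels: (y_post + b·x) − (y_base + b·x) = y_post − y_base. A check on simulated complete data agreed: the interaction estimates were identical with and without the main effect, and moved only when covariate-by-time terms were added.

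**The case against.** The case against has several parts, and most of it stands.

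- **Validity.** A reader might infer that the primary comparison is biased or invalid. It is not: the randomised comparison is unbiased without covariates, and its standard error already allows for chance imbalance. The 21–26% figure holds for any baseline variable in a trial of this size.
- **Proven loss.** A reader might infer that precision is known to be lost. The documents give no R² or correlation, and the prognostic claims rest on cited studies. What counts is variance explained beyond baseline SPADI or NPRS, and the self-efficacy domains overlap in concept with the SPADI domains. The added R² could be small.
- **Power.** A reader might take 77.7% against the stated 80% as a result of omitting covariates. It comes from the sample-size calculation (28 rather than 29 or 30 per arm) and is a separate matter.
- **The second study.** A reader might infer that its ANCOVA does nothing for the group comparison. The text mentions allocated group in that study and does not exclude it from the model, so this goes too far. It remains a separate study and not the stated primary analysis.
- **Detail left to an analysis plan.** Covariate lists often are. But the article is not silent: it fixes the primary model's factors and assigns these two covariates elsewhere. That is a stated choice and can be commented on.

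**Conclusion.** The point holds as a missed efficiency. The plan's own rationale names two predictors and its schedule supplies them at baseline, while its primary model uses neither. The gain cannot be quantified from the documents. Under the stated assumptions (two-sided test, difference 10, SD 13.5 after the baseline score, 28 per arm, two covariates), power would be about 78–85% for R² of 5–20%, against 77.7% without adjustment. The change is nil near 4%, and the worst case is a loss of about 1.6 points (77.7 − 76.1). Correction of a 0.3 SD imbalance would be worth about 0.8–1.6 SPADI points at correlations of 0.2–0.4. The power figures concern SPADI only; the documents give no planning SD for NPRS.

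**What to change.** Amend Statistical analysis to prespecify that the between-group SPADI and NPRS comparison includes baseline expectation as one linear term and one named baseline self-efficacy score (a single domain or a defined combination). State which form is used:

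- an ANCOVA of the post-treatment scores, with the baseline score of the same outcome kept in the model; or
- the repeated-measures model with covariate-by-time terms written out. Some software adds these by default and some does not, so the text should not rely on it.

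Use baseline values only. Third-week expectation and any later value are measured after randomisation and may be affected by treatment. Name the adjusted analysis as primary and report the unadjusted one alongside.

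The cost is a sentence or two and no new data. The statistical price is two degrees of freedom and a small loss of power if the covariates prove weak. Coding the seven-point expectation item as categories would cost up to six degrees of freedom for that item alone, which is why one linear term should be fixed in advance.

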##### Self-efficacy (SE)

SE relates to one’s beliefs that he or she is capable of dealing and executing a certain course of action needed to manage actual and / or prospective events [46]. In health sciences, SE is related to pain and long term incapacity [47], fear of movement [48], and in patients with shoulder pain, is an important factor associated with better therapeutic outcomes [45, 49]. The domains of pain and physical function of the validated Brazilian version of the chronic pain self-efficacy scale will be used in this research [50]. SE will be assessed at baseline, end of the treatment period and on follow-up.

### Participant timeline

The enrollment process will begin from the end of February 2020. After entering the study, participants will have the following outcomes assessed at baseline: SPADI, NPRS, AROM, PPT, expectations and SE; at the end of the treatment period: SPADI, NPRS, AROM, PPT and GROC; and at one month follow-up: SPADI, NPRS, and GROC. Expectation is the only outcome measure to be collected during the third week of treatment. Figure 2 depicts enrolment, interventions and assesssments timeframes throughout the study. Participants will attend ten individual sessions, twice a week (approximately 40 min each), in either of the available treatment sites, according to their geographic locations (see study settings). For the follow-up, participants will be contacted by a research member via email or mail to fill out the respective outcome measures. A telephone call will be made for participants that miss one treatment session without providing explanations.

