**Methods:**

A randomised, sham-controlled trial of 70 adults complaining of RCRP will compare the effects of MWM combined with exercise over sham MWM with exercise. Participants will be allocated to one of two groups: exercise and MWM (EG) or exercise and sham MWM (CG). Two weekly individual treatment sessions will be conducted over five weeks. All assessments will be performed by a blinded assessor. Primary outcome measures will be the shoulder pain and disability index (SPADI) and the numeric pain rating scale (NPRS), assessed at baseline, discharge and one-month follow-up. Secondary outcome measures will be active range of motion, self-efficacy and the global rating of change scale. The analyses will be conducted considering a statistically significant *p*-value ≤0.05. Normality will be assessed with the Kolmogorov-Smirnov test and homogeneity with the Levene’s test. For the primary outcome measures (SPADI and NPRS) and self-efficacy, a 2 × 3 ANOVA with treatment group (EG versus CG) and time (baseline, end of the treatment and follow-up) factors will be performed. Separate 2 × 2 ANOVA will be used for range of motion (baseline and end of the treatment). Global rating scale of change analysis will be conducted using descriptive statistics. Intention-to-treat analysis will be adopted.

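### The participant timeline lists self-efficacy at baseline only, but the outcome section, the statistical analysis and the abstract need it at three time points

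*Protocol article*

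**What the plan says.** The Self-efficacy section under Secondary outcome measures sets three occasions: "SE will be assessed at baseline, end of the treatment period and on follow-up". The Statistical analysis section plans for the same three: "a 2 × 3 ANOVA will be conducted for self-efficacy (baseline, end of the treatment period and follow-up". The abstract groups self-efficacy with the primary measures for this purpose ("For the primary outcome measures (SPADI and NPRS) and self-efficacy, a 2 × 3 ANOVA with treatment group (EG versus CG) and time") and names it as a secondary outcome: "Secondary outcome measures will be active range of motion, self-efficacy and the global rating of change scale". Table 2, the registration data set, also lists it among the key secondary outcomes.

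The Participant timeline goes through the visits one by one. At entry, "participants will have the following outcomes assessed at baseline: SPADI, NPRS, AROM, PPT, expectations and SE". For the two later visits it reads "at the end of the treatment period: SPADI, NPRS, AROM, PPT and GROC; and at one month follow-up: SPADI, NPRS, and GROC". Self-efficacy is in neither list. The only other collection point is closed to it as well: "Expectation is the only outcome measure to be collected during the third week of treatment".

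The same section refers the reader to Figure 2 for the schedule. The figure is not reproduced in the text at hand.

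**The concern.** The timeline gives one self-efficacy measurement and the rest of the article gives three. Both cannot be right. The disagreement matters because the planned analysis is a group-by-time comparison, which needs values after treatment has started. A questionnaire that is not given at a visit cannot be completed retrospectively for that visit, so any loss would be permanent.

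The one-month contact is the most exposed. It is made by email or mail, and participants complete whichever measures belong to that time point. Within the timeline section, the list for that time point omits self-efficacy.

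**Working it through.** No figure in the plan has to be reproduced here. The sample size rests on SPADI and has no bearing on the point. The check is a count of measurement occasions, section against section.

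**Step 1. Occasions per instrument.**

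| Instrument | Its own outcome section | Participant timeline |
|---|---|---|
| SPADI | 3 | 3 |
| NPRS | 3 | 3 |
| AROM | 2 | 2 |
| PPT | 2 | 2 |
| GROC | 2 | 2 |
| Expectations | 2 (start and three weeks) | 2 (baseline and third week) |
| Self-efficacy | 3 | 1 |

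Six of the seven instruments agree. Self-efficacy is the only mismatch. Because the lists are otherwise complete, the timeline cannot be read as a loose selection of measures.

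**Step 2. What the planned analysis needs.** The 2 × 3 ANOVA has 2 groups and 3 times. The group-by-time interaction carries (2 − 1) × (3 − 1) = 2 degrees of freedom.

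**Step 3. What the timeline text would supply.** With baseline only, there is 1 time and the interaction has (2 − 1) × (1 − 1) = 0 degrees of freedom. Two of the three levels of the time factor are empty. No between-group effect after treatment and no within-group change can be estimated. What remains is a comparison of the groups at baseline, which says nothing about treatment.

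**Step 4. Size if the timeline were followed throughout.** For the 70 planned participants, before any dropout, 70 × 3 = 210 self-efficacy assessments are intended and 70 × 1 = 70 would be taken. The shortfall is 70 × 2 = 140, which is all of the post-randomisation values.

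**Step 5. What would survive.** The Statistical analysis section also uses self-efficacy as a covariate in an ANCOVA of SPADI and NPRS for a second study. A baseline value would still serve there. The SPADI and NPRS schedules agree across the outcome sections, the timeline and the analysis, so the primary comparison is untouched.

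**Step 6. After correction.** With self-efficacy added at end of treatment and at one month, the timeline gives 3 of 3 occasions and the planned ANOVA can be run. The sample size does not change.

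**The case against.** The strongest reply is that the intent is plain. The section devoted to self-efficacy, the analysis section and the abstract all agree on three time points, and one prose list is the outlier. Any reader can tell which statement was meant. That is right, and it is why this is best described as a probable omission and not as a poor design choice.

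A second reply is that the schedule proper is Figure 2, which cannot be seen. It may show self-efficacy at all three times. The abbreviation key in its caption does not help: it covers only four measures and also leaves out GROC and expectations, which the timeline does schedule. This reply limits what can be concluded but does not remove the contradiction. If the figure is right, it disagrees with the timeline text. If it matches the timeline text, it disagrees with the outcome and analysis sections.

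A third reply concerns consequence. A reader might infer that site staff will work from the timeline paragraph and that self-efficacy after treatment will therefore be missing for all 70 participants. The article does not support that. It does not say which document or form the assessor uses, and a journal article condenses a fuller protocol. The loss in the working is what would follow if the paragraph were followed, and it is not a forecast.

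**Conclusion.** The inconsistency is real and lies within the article's own text: one self-efficacy measurement in the timeline against three in the outcome section, the analysis section and the abstract. If the timeline text were followed, no post-randomisation self-efficacy would exist and the planned 2 × 3 ANOVA for a listed key secondary outcome could not be run. That consequence is conditional. It assumes that data collection follows the paragraph and that Figure 2 and the forms do not correct it, and neither can be checked here.

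Two stronger readings should be set aside. It would be too much to say that self-efficacy becomes useless, since the baseline value could still be summarised and used as a covariate. It would also be too much to treat this as a threat to the trial's main conclusion, since SPADI, NPRS and the sample size are not involved. This should be fixed, and it ranks below anything that affects the primary comparison.

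**What to change.** - In the Participant timeline, add self-efficacy to the end-of-treatment list and to the one-month list, so that they match the Self-efficacy and Statistical analysis sections.
- Include the self-efficacy scale in the one-month email or mail pack.
- Confirm that Figure 2 and the data collection forms at both sites show self-efficacy at all three times.
- If any participants have already passed a later visit without it, report how many. The article leaves open whether there are any: Table 2 gives the status as recruiting with first enrolment in March 2020, while the Data Availability statement says that the study has not started.

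The planned 2 × 3 ANOVA can stay as it is. The cost is a text correction and one questionnaire (two domains of the scale) at two contacts that already exist, with no new visit and no change in sample size.
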